### Nested qualitative study

#### Design

Maximum variation samples of trial participants and GPs from participating practices will be invited to take part in semi-structured audio-recorded telephone interviews. Patients will be interviewed twice, at approximately 6 and 12 months post-randomisation. GPs will be interviewed once, after completing initial patient recruitment at their practice. Interviews will be conducted after obtaining informed consent and will be anonymised on verbatim transcription. Topic guides comprising open-ended questions and follow-up prompts will be used flexibly to explore individual experiences and perspectives in-depth and to allow novel and unanticipated insights to emerge. Field notes will capture the interviewer’s impressions and reflections. Data collection and analysis will proceed iteratively; the final sample sizes will depend on saturation and when we achieve a rigorous, credible analysis in relation to the qualitative aims.

#### General practitioner interviews

We will aim to interview a diverse range of approximately 30 GPs (full and part-time, sex, rural/urban practice, practice deprivation index, and years as a GP). Interviews will explore GPs’ experiences of the use of amitriptyline prior to and within the trial (in the broader contexts of management of IBS symptoms and other conditions), and potential barriers and facilitators to widespread post-trial implementation in primary care. The topic guide will be informed by relevant literature, key domains from normalisation process theory (NPT) [34], and discussions with the PPI group. NPT provides a framework that specifies the factors and processes likely to hinder or enable widespread implementation of new practices.

#### Participant interviews

We will aim to interview a diverse range of approximately 20 participants from each arm of the trial (to encompass participants from each hub, a mix of sex and ages, a range of baseline symptom severity scores according to the IBS-SSS, and to include those who have decided to continue or stop treatment at 6 months). The interviewer will remain blinded to treatment allocation at the time of the interviews.

The interviews will explore participants’ experiences of recruitment, randomisation, and the trial in general and experiences of initiating and (dis)continuing trial medication and its perceived impacts and changes over time. The 6- and 12-month topic guides will be informed by relevant literature, the common-sense model of illness perception [35], and discussions with our PPI group. The common-sense model provides a framework for understanding how participants experience treatments and make treatment decisions within the context of chronic illness; this has proved relevant in previous qualitative work on IBS [36].

### Sample size

A sample size of 414 evaluable patients will provide 90% power to detect the minimum clinically important between-group difference of 35 points on the IBS-SSS [37], between amitriptyline and placebo at 6 months, assuming a standard deviation of 110 points [38, 39] and 5% significance level. This equates to a small to moderate effect size of 0.32. This 35-point between-group difference was the agreed minimum clinically important between-group difference for the IBS-SSS in another large UK treatment trial in IBS in primary care, the ACTIB trial [37, 40]. The sample size also gives at least 85% power to detect a 15% absolute difference in the key secondary outcome (SGA of relief of IBS symptoms) [24]. Uptake of drugs for IBS that provide a lower therapeutic gain over placebo is less likely [41, 42]. We aim to recruit 518 participants to allow for a 20% loss to follow-up.

### Internal pilot

An internal pilot, commencing in the first month of trial recruitment, across all three hubs, will assess recruitment at 6 months (reviewing rates over the previous 3 months) according to the criteria in Table 2.

**Table 2 Tab2:** Internal progression criteria

Criteria	Green/continue	Amber/review	Red/stop
Monthly recruitment rate (averaged over months 4–6 of internal pilot)	≥ 80% of the target of 28 pts/month: ≥ 22.4	50–80% of 28 pts/month: 14–22.4 pts/month	< 50% of target of 28 pts/month: < 14 pts /month
Follow-up for 6-month primary outcome	≥ 80%	60–80%	< 60%
Outcome of progression review	The study will continue and outcome data from participants in the internal pilot will be included in the main study analysis	A rescue plan will be developed and approved by the TSC before submission to the funder	The TSC will consider not progressing the internal pilot to the definitive study

### Data analysis

#### General considerations

A detailed statistical analysis plan will be written and signed off before the analysis is undertaken. All analyses will be conducted on the intention-to-treat population, defined as all participants randomised, regardless of adherence to the intervention. An overall two-sided 5% significance level will be used for all endpoint comparisons. Outcome data will be analysed once only after data lock, at the final analysis, and no interim analyses are planned.

#### Primary analysis

A linear regression model, adjusted for minimisation variables and IBS-SSS score at baseline, will be used to test for differences between the treatment groups on the IBS-SSS at 6 months. The IBS-SSS is a validated, patient-reported, 5-item questionnaire widely used in trials of medical therapies in IBS [23]. Missing data will be imputed via multiple imputation, where appropriate. Sensitivity analyses on a per-protocol population and on participants with complete data will test robustness of results. Results will be expressed as point estimates, together with 95% confidence intervals and *p*-values.

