#### Randomisation

Randomisation will be performed by the hub research nurse or CSO via an automated system based at the University of Leeds Clinical Trials Research Unit (CTRU). Participants will be allocated to amitriptyline or placebo via minimisation incorporating a random element to ensure the treatment arms are well balanced for depression score (HADS-depression score ≥ 8), predominant stool pattern (diarrhoea, constipation, mixed bowel habit, or unclassified), and hub. Following randomisation, an automatically generated email will be sent to the central pharmacy with instructions to dispense specific trial medication kits, depending on the participant’s allocation, which will be posted directly to the participant.

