#### Secondary analyses

Continuous endpoints at 6 months (HADS, WSAS, and PHQ-12 scores) will be analysed in the same manner as the primary endpoint adjusted for the respective baseline score. Secondary binary endpoints (SGA of relief of IBS symptoms, acceptability of treatment, continuation of trial medication, and adherence) at 6 months will be analysed similarly in logistic regression models.

Additional exploratory analyses of all endpoints at 3 and 12 months will be carried out, as well as repeated measures models incorporating all time points. IBS symptoms reported weekly will be analysed using a repeated measures model. Exploratory moderator analyses will be conducted to investigate if the 6-month treatment effect on the IBS-SSS varies by IBS subtype or mood by including an interaction between the treatment arm and each potential moderator in the primary analysis model.

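### Baseline depression appears to enter the primary model only as the HADS-depression indicator at 8, although the full score is collected; the analysis is valid but gives up a little free precision

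*Protocol article*

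**What the plan says.** All statements are in the protocol article.

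- **Randomisation.** Minimisation balances the arms on "depression score (HADS-depression score ≥ 8), predominant stool pattern (diarrhoea, constipation, mixed bowel habit, or unclassified), and hub". The depression factor has two levels.
- **Primary analysis.** The 6-month IBS-SSS is compared by "A linear regression model, adjusted for minimisation variables and IBS-SSS score at baseline".
- **Secondary analyses, continuous endpoints.** "Continuous endpoints at 6 months (HADS, WSAS, and PHQ-12 scores) will be analysed in the same manner as the primary endpoint adjusted for the respective"; the covariate meant is each endpoint's own score at baseline. A full baseline HADS score therefore exists and already serves as a covariate for the HADS endpoint. Binary endpoints are handled similarly by logistic regression.
- **Secondary analyses, moderators.** An exploratory analysis asks whether the 6-month effect "varies by IBS subtype or mood by including an interaction between the treatment arm and each potential moderator in the primary analysis model". It does not say which score represents mood, or whether that score is continuous or cut.
- **General considerations.** "A detailed statistical analysis plan will be written and signed off before the analysis is undertaken".
- **Sample size.** "A sample size of 414 evaluable patients will provide 90% power" for the "minimum clinically important between-group difference of 35 points on the IBS-SSS", with an SD of 110. The calculation makes no allowance for covariates.

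**The concern.** Read together, the Randomisation and Primary analysis sections leave one depression term in the primary model: the indicator at 8. Participants scoring 8 and 18 are then treated alike, and participants scoring 7 and 8 differently. If baseline depression predicts 6-month IBS-SSS in a graded way, the indicator picks up only part of that relation. The rest stays in the residual variance and slightly widens the confidence interval for the treatment effect. The same holds for WSAS and PHQ-12, whose models follow the primary one. It does not hold for the HADS-depression endpoint if that model carries its own baseline score.

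Balancing on a cut does not oblige the analysis to use only the cut. The baseline IBS-SSS enters as a score, and the depression score is on file as well. A prognostic baseline value already collected is thus left partly unused. What is at stake is efficiency, not validity.

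A second question is whether the mood moderator analysis inherits the cut, because its interaction is added to this same model. That depends on a choice the article does not state.

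**Working it through.** **1. The plan's own figure.** Inputs from Sample size, General considerations and Trial design: difference 35, SD 110, two-sided 5%, 90% power, 1:1 allocation.

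Total N = 4 × [110 × (1.960 + 1.282) / 35]² = 415.2, or 208 per arm (416) after rounding up. With 207 per arm, SE = 110 × √(2/207) = 10.81 and power = Φ(35/10.81 − 1.960) = 89.9%. The stated 414 is reproduced to within rounding, and 414/0.8 = 517.5 gives the 518. No covariate enters this calculation, so the way depression is coded cannot undermine it.

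**2. Information kept by the cut.** Assume a roughly normal HADS-depression score with a share *q* at or above 8. The document gives no *q*; I take 12% to 45%. The squared correlation between the score and its indicator is e = φ(z)² / [q(1 − q)], where z is the normal quantile at 1 − q.

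| q | φ(z) | e (kept) | 1 − e (lost) |
|---|---|---|---|
| 12% | 0.200 | 0.38 | 0.62 |
| 28% | 0.337 | 0.56 | 0.44 |
| 45% | 0.396 | 0.63 | 0.37 |

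**3. Effect on the primary model.** Let *r* be the partial correlation of baseline HADS-depression with 6-month IBS-SSS given the other covariates, taken to be linear. The document gives no *r*; I take 0.1 to 0.3. Residual variance with the full score, relative to the indicator alone, is (1 − r²)/(1 − e·r²). Power is recomputed by treating 110 as the residual SD under the indicator, with 207 per arm. The reference is 89.9%.

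| r | Residual variance reduction (q = 45% to 12%) | Power with full score |
|---|---|---|
| 0.1 | 0.4% to 0.6% | 90.0% to 90.1% |
| 0.2 | 1.5% to 2.5% | 90.4% to 90.6% |
| 0.3 | 3.5% to 5.8% | 90.9% to 91.5% |

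Example at the upper end (r = 0.3, q = 12%): 0.91/(1 − 0.379 × 0.09) = 0.91/0.9659 = 0.942, a 5.8% reduction. The residual SD falls by 2.9%, and power is Φ(3.237/0.9706 − 1.960) = 91.5%, a gain of 1.6 points. Taking q down to 10% gives 91.6%, a gain of 1.7 points. As patients' worth out of 414, the range is about 414 × 0.0037 = 1.5 to 414 × 0.058 = 24.

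These figures apply to the linear models. They do not carry over directly to the logistic models, where adding a prognostic covariate also changes the conditional odds ratio being estimated.

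**4. Moderator analysis, only if mood were the indicator at 8.** For a linear interaction the information kept is again e, so 37% to 62% would be lost and 1/e = 1.6 to 2.6 times as many patients would be needed. The SE of the interaction per SD of score is 2 × 110/√414 = 10.8. For an assumed change of 30 points per SD, power is Φ(30/10.81 − 1.960) = 79% with the score and Φ(30√e/10.81 − 1.960) = 40%, 55% and 60% with the cut at q = 12%, 28% and 45%. For an assumed 10 points per SD, power is 15% with the score and 8% to 11% with the cut.

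**The case against.** Adjusting for a minimisation factor in the form used to allocate is standard and valid. The covariate likely to matter most, baseline IBS-SSS, is already in the model, and the gain from the full depression score is at most a point or two of power. All of that stands. It also argues against replacing the indicator with the score, since that would drop the factor used in allocation.

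A reader might infer two stronger things. The first is that the primary analysis is biased or underpowered. The document does not support this: the indicator introduces no bias, and the 414 takes no credit for covariates.

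The second is that the plan throws away much of the information for the mood moderator analysis. This does not follow either. The text names mood without fixing its form. HADS covers anxiety as well as depression, and an interaction with a full score can be added to the primary model whatever form the minimisation factor takes. The analysis is labelled exploratory, and such coding is commonly left to the analysis plan, which the article says is to be written. The contrast of 79% with 40% to 60% depends on an assumed 30 points per SD, close to the whole 35-point target difference. At 10 points neither version is informative, and a true threshold at 8 would favour the cut.

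Nor should the moderator result be read as a test of the Introduction's suggestion that the drug acts other than through mood. Moderation by baseline mood is a different question from mediation through change in mood.

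What survives is narrow. The covariate set is stated in the article, and it leaves a collected baseline score partly unused.

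**Conclusion.** The point holds as a minor efficiency suggestion. The likely gain in the primary model runs from negligible to modest, and its size rests on the assumed prevalence and partial correlation, an approximately normal score and a linear relation. The type I error, the validity of the treatment comparison and the stated sample size are unaffected. For the moderator analysis the loss is conditional: it arises only if the indicator is chosen to represent mood, and the document neither says so nor rules it out.

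**What to change.** In the analysis plan, before sign-off:

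1. Keep the minimisation indicator at 8, stool pattern, hub and the baseline outcome score, and add continuous baseline HADS-depression as a covariate in the primary model and the secondary models that follow it. Where the endpoint is HADS-depression itself, its own baseline score already does this.
2. State that the mood moderator analysis uses a treatment-by-continuous-score interaction, name the HADS score or scores meant, and keep the split at 8 for descriptive display only.

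The cost is a few lines of wording and one degree of freedom per model for the added covariate. No new data are needed, and randomisation and sample size do not change.

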#### Secondary analyses

Continuous endpoints at 6 months (HADS, WSAS, and PHQ-12 scores) will be analysed in the same manner as the primary endpoint adjusted for the respective baseline score. Secondary binary endpoints (SGA of relief of IBS symptoms, acceptability of treatment, continuation of trial medication, and adherence) at 6 months will be analysed similarly in logistic regression models.

Additional exploratory analyses of all endpoints at 3 and 12 months will be carried out, as well as repeated measures models incorporating all time points. IBS symptoms reported weekly will be analysed using a repeated measures model. Exploratory moderator analyses will be conducted to investigate if the 6-month treatment effect on the IBS-SSS varies by IBS subtype or mood by including an interaction between the treatment arm and each potential moderator in the primary analysis model.

#### Safety analyses

All participants receiving at least one dose of trial medication will be included in the safety analysis. Descriptive statistics of self-reported AEs on the ASEC will be presented by arm. The number of participants reporting a SAE and details of all SAEs will be reported for each treatment group. The number of participants withdrawing from trial treatment will be summarised by treatment arm, along with reasons for withdrawal.

#### Cost-effectiveness analyses

A within-study cost-effectiveness analysis will be conducted adopting the perspective of the NHS and Personal Social Services and a societal perspective. The time horizon will be 6 months; hence, costs and outcomes will not be discounted. The primary outcome will be cost per QALY. We will assess uncertainty using a within-trial probabilistic sensitivity analysis undertaken using Monte Carlo simulation, with results presented as incremental cost-effectiveness ratios and cost-effectiveness acceptability curves, assuming a willingness to pay (lambda) of £20,000 per QALY. Sensitivity analyses will include a 12-month horizon, as well as a scenario as close as possible to a real NHS context, where the treatment is prescribed by the GP with repeated prescriptions, tests, and required appointments. Health economic analyses will be subject to further funding (protocol v5.0).

#### Qualitative analysis

Interviews will be transcribed verbatim (by professional transcribers and/or the research team) and transcripts will be anonymised. Transcripts will be imported into NVivo to facilitate data management and record-keeping. We will employ established techniques to enhance the quality and credibility of our analysis, including maintaining an audit trail to ensure transparency, involving multiple individuals — including PPI representatives — to ensure diverse perspectives are brought to bear on the data and avoid idiosyncratic interpretations, and deliberately seeking out anomalous or “deviant” cases and using them to identify important, but rare, views and the limits of the analysis. Our themes will be based on importance and relevance, not prevalence, consistent with best practice in qualitative research involving in-depth analysis of small, diverse samples.

Thematic analysis [43] will proceed separately for GP and patient interviews and will be augmented with coding techniques from grounded theory (e.g. open coding, line-by-line coding, constant comparison) [44]. Analysis will be primarily inductive, but we will draw on NPT (GP interviews) and the common-sense model of illness perception (patient interviews) to assist in interpreting findings related to wider implementation of amitriptyline for IBS in primary care and participants’ experiences of IBS and its treatment. For patient interviews, after having identified initial themes, and final trial unblinding, we will construct cross-tabulations (“matrices”) of themes by trial arm to help us relate the qualitative findings to the quantitative results.

### Patient and public involvement

The trial team includes a co-applicant and provides patient and public involvement (PPI) representation on the Trial Management Group (TMG) who leads a local IBS support group and a PPI officer who leads on the development and implementation of PPI throughout this study. In addition, there is PPI representation on the Trial Steering Committee (TSC), to ensure that a patient perspective is included in all decisions related to the trial. Patients will advise on design considerations, patient leaflets, invitation letters, recruitment strategies, the trial protocol, and dissemination activities. PPI will also be key in guiding the development of GP and patient interview topic guides. During recruitment, PPI perspective will be sought on emerging issues. We will offer free places on the CTRU “Introduction to Clinical Trials” training and financial reimbursement will be offered in line with INVOLVE guidance.

### Research governance

Trial supervision will be established according to the principles of GCP and in-line with the UK Policy Framework for Health and Social Care Research. This will include the establishment of a core project team, TMG, TSC, and DMEC.

The trial is managed on a day-to-day basis by the CIs and a core team at the Leeds CTRU. The TMG comprises the CIs, all co-applicants, hub study nurses or CSOs, the CTRU team, and the PPI representative, who meet monthly to review progress.

Independent oversight is provided by the TSC and DMEC. The TSC meets at least annually and is responsible for providing overall supervision for the trial in accordance with pre-agreed terms of reference, particularly trial progress, including completion of the internal pilot according to pre-defined success criteria and adherence to the protocol. The DMEC receives 6-monthly unblinded safety summaries and meets the trial team annually to monitor study conduct, participant safety, and unblinded data, in accordance with pre-agreed terms of reference. The DMEC may recommend discontinuation of the trial if significant ethical or safety concerns arise prior to trial completion.

### Monitoring and audit

As this trial is using a drug (amitriptyline) with a well-established safety profile and at a low dose, all monitoring for this trial will be done centrally at the CTRU throughout the conduct of the trial, with site monitoring only occurring for cause-triggered visits only.

### Confidentiality

All participant information collected during the trial will be kept confidential, in compliance with the 2018 Data Protection Act. Participant information will be held on a secure password-protected database. All trial documentation will be held in secure offices. At the end of the trial, all data held by the CTRU, and all trial data will be securely archived at the University of Leeds in line with the trial sponsor’s procedures. Access to trial data will be subject to agreement with the Leeds CTRU and the ATLANTIS CIs, through a legally binding contract with the University of Leeds.

### Dissemination policy

Results of the trial will be disseminated via traditional academic routes and by social media and patient groups. Authorship guidelines will be developed. Results will be presented at national and international primary care and gastroenterology meetings and, therefore, will be cascaded to GPs and gastroenterologists. As well as being published in the publicly available HTA journal, we plan to publish our research in high-impact, high-quality, multi-disciplinary journals. With the help of our PPI group, we will produce plain English summaries and podcasts of findings available online for relevant patient groups and trial participants.

## Discussion

The ATLANTIS trial will be the first RCT of amitriptyline in IBS to be conducted in primary care, and the largest trial of a TCA for IBS to date. This trial will have a real impact on clinical practice, as it will identify whether amitriptyline is effective for the management of IBS in this setting, improving the management of IBS in primary care. If effective, amitriptyline may improve symptoms, quality of life for patients and, ultimately, lower overall costs to the health service for the management of IBS. If amitriptyline is cost-effective as a second-line management strategy for IBS, then this will have important implications for the health service.

The challenges we expect this trial to present mainly relate to patient recruitment and retention. Early discussions with PPI identified the possible reluctance some patients may have to take amitriptyline. Amitriptyline is most well recognised as an antidepressant drug. However, these effects are present at doses much higher than the maximum dose of 30 mg being used in this trial. The usual doses to treat depression are 75 to 150 mg/day and up to 225 mg to 300 mg/day for severe resistant depression. Our PPI activity made recommendations to ensure understanding of the rationale for its use in IBS and was involved in developing clear written guidance on how to dose titrate, as well as education about potential side effects, which will hopefully tackle potential misconceptions, increase adherence to trial medication, and minimise drop-outs.

